# Pilot study of physiotherapist-led versus music therapist-led breathing control exercises for young adults living with breathing pattern disorder: a randomised controlled trial protocol

**DOI:** 10.1136/bmjresp-2022-001414

**Published:** 2022-09-14

**Keywords:** perception of asthma/breathlessness

## Abstract

**Introduction:**

Breathing pattern disorder (BPD) is an abnormal breathing pattern associated with biochemical, biomechanical and psychophysiological changes. While physiotherapy is often offered, limited evidence-based therapies for BPD are available. Music therapy-based singing exercises have been shown to improve quality of life for individuals with respiratory conditions and may also be beneficial for individuals living with BPD. No study has previously compared these participatory interventions in the treatment of people living with BPD.

**Methods and analysis:**

This is a study protocol for an assessor blinded 1:1 randomised controlled trial and qualitative interview study. Forty participants aged 18–40 years who score at least 19 on the Nijmegen Questionnaire (NQ) and do not have any underlying respiratory conditions will be recruited. Participants will be randomised to receive either physiotherapy-led or music therapy-led breathing exercises for 6 weeks. The primary outcome will be between-group difference in NQ post-intervention. Semistructured interviews with a purposive sample of participants will be performed. Qualitative data will be analysed using thematic analysis to better understand participants’ intervention and trial experiences.

**Ethics and dissemination:**

This study has received ethical approval by Brunel University London College of Health, Medicine and Life Science’s Research Ethics Committee (32483-MHR-Mar/2022-38624-3). The anonymised completed dataset will be made available as an open-access file via Brunel University London Figshare and the manuscript containing anonymised patient data will be published in an open-access journal.

**Trial registration number:**

This trial is registered on the Open Science Framework Registry (https://osf.io/u3ncw).

What is already known on this topicBreathing pattern disorders (BPDs) are prevalent in young adults with limited evidence-based therapy options available.What this study addsThis protocol details two interventions which will be compared for their effectiveness for the first time.Novel participant experiences of these interventions will also be explored.How this study might affect research, practice or policyThis protocol will establish interventions which can be reproduced in future studies.If both physiotherapy and music therapy are considered effective in treating BPD in the absence of underlying respiratory disease, this research could be considered for inclusion in future treatment guidelines.

## Introduction

Breathing pattern disorder (BPD), otherwise known as dysfunctional breathing (DB), is defined as having an abnormal breathing pattern according to alterations in breathing timing, coupling to movement, the passage of air in and out of the respiratory system, distribution of breathing and focus of attention.^1^ While there is ongoing discussion about the exact definition of what constitutes BPD, it is widely recognised that BPD is multifaceted, being associated with biochemical, biomechanical and/or psychophysiological changes.^2–6^ Specifically, regarding the biochemical dimension, people may experience disturbances in blood pH homeostasis. Biomechanical changes include alterations in respiratory mechanics, muscle tone, strength, coordination and the use of the nose or mouth for breathing. Finally, on a psychophysiological level, BPD seems to be associated with specific maladaptive thoughts, feelings, breathing behaviours and symptoms.^2^ Taken together, BPD includes both subjective and objective breathing pattern changes, and can therefore substantially impacts a person’s quality of life.^7–13^ However, not all BPDs combine all biochemical, biomechanical and psychophysiological changes. Estimates of BPD’s prevalence vary, but it has been reported to occur in 8% of adults with a mean age of 44^14^ to 22% in young adults with a mean age of 21,^12^ while secondary (ie, due to underlying pathology) BPD may affect up to a third of adults with asthma.^14^ Outcomes used to measure BPD include cardiopulmonary exercise testing,^15^ the Manual Assessment of Respiratory Motion (MARM),^16^ the Self-Evaluation of Breathing Questionnaire (SEBQ),^17^ the Nijmegen Questionnaire (NQ)^1 10 18^ and the Breathing Pattern Assessment Tool (BPAT).^11^ Neither the NQ or BPAT outcomes have established minimal clinical important differences related to the comparison of interventions but are commonly used and combine inexpensive participant and assessor analysis of breathing pattern subjectively and objectively.

Limited evidence-based therapies for BPD are available. Current standard care is the provision of breathing exercises delivered by a physiotherapist. Evidence shows that clinical benefits are achieved with physiotherapist-led breathing exercises for individuals with secondary BPD.^9 19–21^ However, a high-quality evidence for these interventions is limited,^22^ particularly for individuals with primary dysfunctional breathing in the absence of other pathology. Singing for Lung Heath (SLH) is an intervention designed to enable people with chronic respiratory disease to use singing exercises and repertoire to enable them to manage their symptoms.^23^ Music therapy simultaneously targets physiological and psychological changes to help improve control of breathing.^24–27^ SLH has been shown to be beneficial at improving the quality of life and perceived breathing control of patients with chronic obstructive pulmonary disease in a UK-wide service evaluation, and in studies with comparison groups receiving no active intervention, or alternative group social interaction in chronic obstructive pulmonary disease (COPD).^23 28–30^ Forty-seven per cent of individuals with COPD have secondary BPD.^31^ Singing interventions may also be applicable and beneficial for individuals living with primary BPD. Singing-based exercises have also been shown to help improve the mental health component of quality of life and perceived exertional breathlessness for those with persistent symptoms post COVID-19.^32^ The proposed pilot study will explore whether there are any significant differences in measures of breathing pattern and related patient-reported outcomes between physiotherapist-led breathing control exercises (as provided in ‘standard’ care) compared with music therapist-led breathing control exercises for individuals living with primary BPD. Data analysis will inform sample size calculations for a more definitive trial.

This manuscript has been prepared according to the Standard Protocol Items: Recommendations for Interventional Trials 2013 checklist.^33^

## Methods and analysis

### Population

We aim to recruit 40 young adults aged between 18 and 40 years who have BPD, using Brunel University London Research Participation website, posters placed around campus and via investigator and Brunel University affiliated social media accounts. This sample size is in line with previously recommended ranges for pilot and feasibility designs.^34 35^ This is an assessor blinded 1:1 randomised controlled trial (RCT) pilot study with qualitative interview substudy.

Inclusion criteria are as follows:

Young adults between 18 and 40 years with a score of at least 4 on the BPAT^11^ or at least 19 on the NQ.^18^ BPDs are common in younger populations^12^ and we want to optimise the interventions based on findings in this study before testing in potentially more frail populations. Both outcomes will be used as there is no single gold standard diagnosis for BPD.Access to an internet-enabled device.Normal spirometry according to forced expiratory volume in the first second (FEV_1_) and forced vital capacity (FVC) above 80% of that predicted for age, height, sex and race.

Exclusion criteria are as follows:

Previously received one-to-one singing tuition or physiotherapy led breathing control exercises.Previously or currently member of a choir.Diagnosis of other respiratory diseases which may lead to BPD (i.e., Asthma, COPD, long COVID, Bronchiectasis, Interstitial Lung Disease, chronic cough, sinus disease).Diagnosis of neurological disease which impacts on respiratory system.Unable to provide consent.Pregnant

## Recruitment

### Online screening

Participants who register their interest to participate in the study will be sent an email asking them to complete the NQ,^10^ a patient-reported outcome measure that assesses functional respiratory complaints.^1 24^ The NQ has become the standard outcome measure used to identify BPD. Only participants who score at least 19 at screening^1 18^ will continue onto the study and repeat the questionnaire at their baseline assessment and post therapy.

### Consent

Face-to-face informed consent will be obtained prior to any study assessment or intervention taking place. The investigator or designee will explain that the participants are under no obligation to enter the trial and that they can withdraw at any time during the trial, without having to give a reason. A copy of the signed informed consent form will be given to the study participant. The original signed consent form will only be accessible to members of the study staff.

### Face-to-face baseline/screening assessment

Assessments will be performed by an individual who has received training in breathing pattern assessment. The assessment will include the following:

Medical history, medication history, social history and demographic information such as age, sex, height and weight will be recorded. Next, screening and baseline spirometry will be performed using a portable spirometer (Micromedical Microlab 3500 Mk8) according to international guidelines.^36^ Should any abnormal finding become present following the spirometry, that is, FEV_1_ or FVC under 80% predicted, repeat spirometry may be indicated. Should abnormal findings be repeated individuals, will not continue into the study and the participant will be encouraged to contact their General Practitioner.

The participant will then complete the following outcomes:

The Nijmegen Questionnaire as described above.

The Breathing Hypervigilance Questionnaire (Breathe-VQ) is a six-question Likert scale response questionnaire. It has been developed by the current study team and has shown to have good construct validity, internal consistency and test-retest reliability in a study comprising of young dysfunctional breathers and non-dysfunctional breathers.^37^ The Breathe-VQ screens for the presence of excessive anxious, conscious monitoring of breathing state (‘hypervigilance’), which is thought to potentially contribute to the experience of breathlessness.^38^ Our hypothesis is that the interventions could also indirectly help to improve breathing pattern by reducing such vigilance and awareness. The Breathe-VQ will be used as a secondary outcome measure exploring its responsiveness to change post intervention for the first time.

The Breathing Pattern Assessment Tool: This is a clinician-led assessment of BPD.^11^ The clinician scores between 0 and 2 for different areas of assessing breathing pattern, including abdominal/chest movement, inspiratory flow, expiratory flow, channel of inspiration (nose or mouth), air hunger, respiratory rate and rhythm. The higher the score, the worse the breathing pattern. A score of at least 4 indicates BPD. Individuals will be asked which time of year their breathing is worse, and if there are any significant triggers for their BPD.

Participants who score at least 19 on the NQ or 4 on the BPAT will continue onto the study. Participants who do not record a score of at least 19 on the NQ or 4 on the BPAT will be excluded from the study at this stage. This information will be important to plan for a future definitive study. Participants will complete the Breathe-VQ, followed by the NQ, and a trained research assistant will then perform a BPAT in that order.

In total, the baseline screening/assessment will last approximately 1 hour.

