##### Insight into effect of interventions

Percentage of participants in each arm who are deemed recovered post-therapy (less than 17) and therefore no longer diagnosed with BPD.^41^Percentage of participants in each arm who demonstrate clinically relevant change in the NQ (at least 10 points).^41^Between-group differences in Breathe-VQ questionnaire.Between-group differences in BPAT scores.

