### Statistical analyses

Forty participants is considered to be a suitable sample size for intervention pilot studies.^44^ This number of participants accounts for a likely small effect size between groups and an 80% powered definitive trial.^45^

For continuous outcome data from questionnaire data, data will be presented as mean (SD) or median (range). Comparisons will be made using a two-way repeated measures analysis of variance (ANOVA), with group as the between-participants factor and timepoint as the within-participants factor. This will be followed by post hoc t-tests if interaction is significant. Non-parametric data will be analysed using generalised estimation equation modelling. All tests will be two-sided and with alpha set at 0.05. Cohen’s *d* and *r* effect sizes will be calculated for parametric and non-parametric tests, respectively. We will also present a sample size calculation for a future definitive trial based on the primary outcome NQ results, and results regarding screening, recruitment and drop-out rates.

Additional exploratory analysis will be performed of between-group differences for the BPAT and Breathe-VQ due to the novelty of using these outcome measures in this population and because they may have important additional information on domains that are relevant to BPD.

No interim analyses are planned.

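### The analyses that name the Breathe-VQ compare two active arms, whereas its stated purpose, responsiveness to change, needs the pooled pre-post change and its relation to symptom change

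*Protocol article*

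**What the plan says.** All references are to the protocol article.

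- **Purpose.** Under Face-to-face baseline/screening assessment, the Breathe-VQ is made a secondary outcome measure, "exploring its responsiveness to change post intervention for the first time". The same paragraph hypothesises that the interventions, in the plural, may work partly by lowering vigilance.
- **Outcome list.** Under Insight into effect of interventions, the Breathe-VQ entry is "Between-group differences in Breathe-VQ questionnaire".
- **Exploratory analysis.** Under Statistical analyses: "Additional exploratory analysis will be performed of between-group differences for the BPAT and Breathe-VQ".
- **General model.** The same section covers questionnaire outcomes as a class: "For continuous outcome data from questionnaire data, data will be presented as mean (SD) or median (range"). It compares them by two-way repeated measures ANOVA, "with group as the between-participants factor and timepoint as the within-participants factor". On post hoc testing it says: "This will be followed by post hoc t-tests if interaction is significant". On error rate: "All tests will be two-sided and with alpha set at 0.05".
- **Design.** Forty participants are randomised 1:1 to two active therapies of similar dose and contact time. The between-group effect is expected to be small. All baseline measurements are repeated at follow-up.

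**The concern.** Responsiveness is the property that a score moves when the person's condition moves. To study it one needs the change within people and, ideally, evidence that this change follows change on another measure of the condition. A contrast between two therapies answers a different question, namely whether one moves the score more than the other.

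Both arms here are expected to help, and the protocol hypothesises that both could reduce vigilance. Equal improvement is thus a plausible result, and in that case the between-group contrast is expected to be null for a responsive and an unresponsive questionnaire alike. Yet it is the only Breathe-VQ result that the outcome list and the exploratory paragraph ask for.

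The pilot is meant to inform a definitive trial. If the Breathe-VQ result is reported mainly as no difference between groups, it may be taken as evidence that the instrument does not respond, which that contrast cannot show.

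**Working it through.** **1. Plan's own figure.** There is none to reproduce. The sample size of 40 rests on cited pilot-study recommendations, and the article gives no effect size, SD or target for the Breathe-VQ.

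**2. What the planned ANOVA shows if both arms improve equally.** From the article: 20 per arm, two timepoints, two-sided alpha 0.05. Assumed: a common improvement of 0.2 to 0.8 baseline SD and a pre-post correlation of 0.5 or 0.7. Rejection rates from 20,000 simulated trials per scenario:

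| Common improvement (baseline SD) | Group-by-time interaction | Group main effect | Time main effect (correlation 0.5 to 0.7) |
|---|---|---|---|
| 0.2 | about 5% | about 5% | 24% to 36% |
| 0.3 | about 5% | about 5% | 45% to 67% |
| 0.5 | about 5% | about 5% | 87% to 98% |
| 0.8 | about 5% | about 5% | over 99% |

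At 13 per arm (about 66% of 20, the article's completion threshold), the time effect at 0.5 SD is detected 69% to 88% of the time.

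The between-group terms stay at alpha whatever the improvement, so they carry no information on responsiveness here. The time term does carry information on pre-post change.

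**3. Link between the time effect and a responsiveness index.** The standardised response mean (SRM) is mean change divided by SD of change. With improvement d in baseline SDs and pre-post correlation ρ, SRM = d / √(2(1 − ρ)). For d = 0.5:
- ρ = 0.5: 0.5 / √1 = 0.50
- ρ = 0.7: 0.5 / √0.6 = 0.65

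With equal arms, two timepoints and the SD of change pooled within arms, SRM = √(F_time / N). The planned model therefore already contains this quantity; it is just not named or assigned to the aim.

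**4. Precision of the SRM.** SE = √(1/n + SRM²/(2n)); 95% CI = SRM ± 1.96 × SE. The SRM values are assumptions; n = 26 is about 66% of 40.
- SRM 0.8, n = 40: SE = √(0.025 + 0.64/80) = 0.182; CI 0.44 to 1.16
- SRM 0.8, n = 26: SE = √(0.0385 + 0.64/52) = 0.225; CI 0.36 to 1.24
- SRM 0.5, n = 40: SE = √(0.025 + 0.25/80) = 0.168; CI 0.17 to 0.83
- SRM 0.5, n = 26: SE = √(0.0385 + 0.25/52) = 0.208; CI 0.09 to 0.91

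**5. Precision of the correlation of Breathe-VQ change with NQ change.** Fisher z: atanh(r) ± 1.96/√(n − 3), transformed back. The r values are assumptions.
- r = 0.5, n = 40: 0.549 ± 0.322 = 0.227 to 0.872; r from 0.22 to 0.70
- r = 0.5, n = 26: 0.549 ± 0.409 = 0.141 to 0.958; r from 0.14 to 0.74
- r = 0.3, n = 40: 0.310 ± 0.322 = −0.013 to 0.632; r from −0.01 to 0.56
- r = 0.3, n = 26: 0.310 ± 0.409 = −0.099 to 0.718; r from −0.10 to 0.62

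A moderate correlation would be distinguishable from zero, even at the completion threshold; a weak one would not.

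**The case against.** The strongest reply is that the general ANOVA already answers the question. The Breathe-VQ is a questionnaire, it is repeated at follow-up, and timepoint is a factor in the model. If both arms improve, the trial would report a time effect without an interaction, which says that people changed. This stands, and it rules out two stronger readings:

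- A reader might infer that the plan makes only between-group comparisons and would come out null if both therapies work. The time effect contradicts that, as step 2 of the working shows.
- A reader might infer that change within arms is reported only after a significant interaction. The text restricts post hoc t-tests, not reporting; means with SDs, or medians with ranges, are presented in any case. With two timepoints and no interaction, the pooled time effect is the natural summary.

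It is also fair to say that responsiveness appears in one clause about a secondary measure, that the main study aim is the comparison of therapies, and that a named index could sit in a fuller document that is not shown. A missing index would be a weak point by itself. The article is not silent, however: it states a purpose and then twice names a Breathe-VQ analysis that does not serve it.

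The reply does not reach two matters. Nothing links the time effect to the responsiveness aim. And with no untreated arm, a time effect cannot separate treatment response from natural change or regression to the mean, so by itself it is weak evidence of responsiveness. No planned analysis sets Breathe-VQ change against change in symptoms.

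**Conclusion.** The point holds as a mismatch between a stated aim and the analyses named for it. The between-group contrasts do not measure responsiveness and are expected to be null under equal benefit. The planned time effect supplies part of what is needed, but it is not assigned to the aim, and the relation to symptom change is absent.

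Priority is minor. The matter is secondary and exploratory and does not touch the primary outcome, the sample size or the feasibility criteria. The power and precision figures rest on assumed improvements, correlations and SRMs that the article does not give.

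The added analysis would have limits of its own. Entry is selected on the NQ, so NQ change includes regression to the mean and is an imperfect anchor. With no untreated control, the results would describe how the two scores move together after therapy and would not prove a treatment effect on vigilance.

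**What to change.** In Insight into effect of interventions and in Statistical analyses:

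1. State that responsiveness of the Breathe-VQ is assessed, pooled over arms, by the SRM of pre-post change with 95% CI, taken from the ANOVA time effect, and by the correlation of Breathe-VQ change with NQ change, with 95% CI.
2. Keep the between-group Breathe-VQ difference as a separate question, and say that a null result there is not evidence of poor responsiveness.
3. Note the two limits on interpretation: selection on the NQ at entry, and no untreated control.

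The cost is a few lines of wording. All the data are already collected at baseline and follow-up, and participants carry no added burden.

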### Randomisation

Following the baseline screening/initial assessment, individuals will be randomised on a 1:1 basis based on a computer-generated random sequence generated using random.org, either to music therapist-led breathing exercises or physiotherapy-led breathing exercises (the next subsection details these interventions). Randomisation will be performed by an independent member of staff not involved in baseline or follow-up assessments and confirmation of group allocation will be provided online. The assessor will be blinded to which group the participants have been randomised to. Participants will be instructed to not disclose which intervention arm they have been allocated to. Should their intervention become known to the assessor at any time, another researcher will perform the follow-up assessment. Due to the nature of the interventions, it is impossible to blind participants to the intervention.

### Intervention details

Participants will be randomly assigned to one of the following two interventions:

#### Intervention A

Music therapist-led breathing exercises: One-to-one face-to-face breathing exercises will be led by a music therapist (HCPCreg). Exercises will be based on previously established core components of SLH exercises which have established intervention fidelity and for which no serious adverse events have been reported in previous studies.^23 39^

